### Control group

During the entire study, the control group receives only measurements according to the same protocol and time plan as for the intervention group. The parents are informed about the results of the measurements after completion of the study. In case parents request more information on passive smoke exposure in children, they are encouraged to contact their general practitioner.

### Outcomes

An overview of the measurements is provided in Table 2. All measurements are home-based and all questionnaires are completed by the parents.

**Table 2 T2:** Overview of the outcome measurements

	***Time (months)***	**0**	**3**	**6**	**9**	**12**
***Outcome measures***						
**Measurements:**						
Urine cotinine		●	●	●	●	●
Household nicotine level		●				●
EBC		●		●		
Wheezometer		●		●		
Long function		●	●	●	●	●
**Questionnaires:**						
Parental smoking behaviour [24], PS exposure to the child Beliefs about PS exposure in children		●	●	●	●	●
Respiratory symptoms and infections (based on questions developed by the PREPASE team and the respiratory symptoms questionnaire [37]		●	●	●	●	●
ISAAC [23]		●				●
Quality of life (FSII) [38]		●	●	●	●	●
Process evaluation						●

The measurements take place in both groups of the RCT, all measurements are home based. The process evaluation questionnaire is completed only in the intervention group. Questionnaires are completed by the parents. PS = passive smoke.

### Primary outcome measures

#### Eliminating or reducing PS exposure in children

PS exposure is measured with a standard questionnaire (at baseline and at 3, 6, 9, and 12 months after the baseline measurement) and is checked by urine cotinine concentrations of the children. In the PREPASE study, the percentage of parents eliminating or reducing PS exposure in children at home at 6 months (directly after the intervention program) is compared between the intervention and the control group. Eliminating or reducing PS exposure in children can be achieved ideally by parents stopping active smoking or less ideally by parents smoking outside the house.

PS exposure in children is measured with the following questions: “Do you smoke in the presence of your child?” (yes/no) If yes, “Where do you smoke in the presence of your child and does this occur always, regularly, sometimes or never?” (Parents are asked to provide an answer for the following locations: living room, own bedroom, child’s bedroom, kitchen, under the hood, hall, dining table/room, attic, rest/bathroom, balcony, garden, car, other) “On average, how many tobacco products do you smoke per day in the house while your child is present at the moment?” (xx cigarettes/cigars/pipe per day) “On average, how many tobacco products do you smoke per day outdoors while your child is present at the moment?” (xx cigarettes/cigars/pipe per day). Furthermore, parental report is verified by the child’s urine cotinine concentration.

#### Urine cotinine of the children

Cotinine is the major metabolite of nicotine and can be detected in several bodily fluids, such as blood serum, saliva and urine [33]. Urine samples are collected (at baseline and after 3, 6, 9, and 12 months after the baseline measurement) and analysed for cotinine using the gas chromatography–mass spectrometry technique, Thermo Scientific DSQIII (Axel Semrau GmbH & Co. KG, Sprockhövel, Germany). Samples from children who have not yet been trained to go to the toilet are collected by placing a highly absorbent cotton wool in the diapers. Samples from toilet trained children are collected with a standard urine collection cup. Early-morning urine samples are collected on the day of the measurements by the RA or primary researcher. The urine samples are analysed at Medical Laboratory Humicon, B.V., Maastricht, the Netherlands. The laboratory receives the urine samples on the same day and stores them at 2-8° Celsius and analyses them within 1–2 weeks. The samples are provided with a numerical ID, the child’s birth year, date and time of collection. The laboratory is blinded to subjects’ identity and group assignment.

### Secondary outcome measures

#### Parental smoking behaviour

Parents active smoking behaviour is measured (at baseline and at 3, 6, 9, and 12 months after the baseline measurement) with a standard questionnaire [24] and questions related to PS exposure in children (in addition to the questions above, parental attitudes, normative and self-efficacy beliefs concerning the prevention of PS exposure in children are also assessed) (see Additional file 1). When applicable, both parents are asked to complete the questionnaire.

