### Our secondary research questions are

1. Does eliminating or reducing PS exposure in children persist after the intervention program (measured at 9 and 12 months of follow-up)?

2. What is the effect of the intervention on parents’ active smoking? Will the intervention also lead to smoking cessation?

3. What is the influence of PS exposure in children with high risk of asthma on their lung function, inflammatory markers in exhaled breath and respiratory complaints?

The aim of this article is to describe the PREPASE study design, which could benefit others who are planning comparable intervention programs.

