**Figure 1 F1:**
[figure not shown]
**Flowchart of the PREPASE study.** BM = baseline measurement. M = Measurement. The first session starts 1 month after the BM and take place once per month during 6 months. The measurements take place every 3 months after the BM.

Blinding of participants or members of the research team for this study is not possible. However, prior to randomization the participants receive limited information on the intervention program. Participants are informed that the study aims at testing a program to help parents prevent PS exposure in their children and to study the relationship between PS exposure and respiratory complaints in children.

After randomization, parents receive more information about their group allocation. All visits are planned for the entire study period, and a confirmation letter is sent to the participants including information and materials with instructions for the urine sampling and lung function measurements in children.

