
In the beginning, parents are told that our primary focus is on preventing PS exposure in children, and that quitting active smoking is not required. The intervention is tailored to whether parents are interested in reducing and/or eliminating PS exposure in their children, or if they are interested in quitting active smoking as well. If both parents of a child smoke, they are counselled together to enable a long-lasting intervention effect. If only one parent smokes, the other parent is still requested to be present during the session. The non-smoker parent may motivate the smoking parent or and reinforce his or her goals to prevent or eliminate PS exposure in their child. If parents permit, the counselling sessions are recorded on audio. The purpose of the recordings is to randomly examine the treatment fidelity. Although the intervention is tailored, a counselling protocol is developed to serve as a guideline for the counselling sessions. The following subjects are discussed:

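### Secondary question 2 (smoking cessation) rests on parental self-report alone in an unblinded trial that counsels one arm, so unequal over-reporting could produce a false cessation effect; label the result and add a contradiction check

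*Protocol article*

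**What the plan says.** **The question.** The second of the protocol's secondary research questions concerns parents' active smoking and asks: "Will the intervention also lead to smoking cessation".

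**The measurement.** Among the secondary outcome measures, the protocol states how this is assessed: "Parents active smoking behaviour is measured (at baseline and at 3, 6, 9, and 12 months after the baseline measurement) with a standard questionnaire". The Outcomes section adds that "all questionnaires are completed by the parents". Where applicable both parents fill it in. Table 2 lists no biological test of the parents.

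**The existing verification.** The sections on the primary outcome and on statistical methods check parental report against the child's urine cotinine, but only for the child's exposure. The protocol links cessation to that outcome: "Eliminating or reducing PS exposure in children can be achieved ideally by parents stopping active smoking". The same sentence names smoking outside the house as a second, less ideal route.

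**Blinding and contact.** Under Randomisation: "Blinding of participants or members of the research team for this study is not possible". The intervention is six home sessions. Its content is tailored to whether parents want to reduce or eliminate the child's exposure, "or if they are interested in quitting active smoking as well", although parents are told at the start that "quitting active smoking is not required". For the comparator, "the control group receives only measurements according to the same protocol and time plan as for the intervention group".

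**Error control.** Secondary outcomes are tested at 1%.

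**The concern.** A parent who has had six hour-long conversations at home about smoke and the child, with the same research assistant, may feel more pressure to report having quit than a parent who was only measured. If so, the reported cessation rates differ between arms even when true cessation does not. The 1% level guards against chance findings across many outcomes; it does nothing about a difference built into the reports. The trial could then answer its cessation question with a positive result that reflects reporting alone.

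Data that could expose some false claims are already collected in both arms: child urine cotinine at every measurement visit, and living-room nicotine at months 0 and 12. The protocol does not plan to use either for this question.

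**Working it through.** **The plan's own figure.** For 10% v 30%, two-sided 5%, 80% power, pooled-variance formula:

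n per arm = [1.960·√(2·0.20·0.80) + 0.842·√(0.10·0.90 + 0.30·0.70)]² / 0.20² = 61.6, so 62 per arm, 124 in total. The protocol states 126, which is close enough to count as reproduced. With dropout, 126/0.85 = 148.2; the protocol states 148. I take 126/2 = 63 analysed families per arm.

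**Model for misreporting.** Let c be the true cessation rate, the same in both arms (no true effect). Let f and g be the proportions of continuing smokers who claim to have quit in the intervention and control arms. The reported rates are:

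- intervention: c + (1 − c)·f
- control: c + (1 − c)·g

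From the protocol: 63 per arm and the 1% level. Assumed, because the protocol gives no values: c, f and g. The test is a pooled two-sided chi-square on one cessation status per family, evaluated by exact enumeration of both binomials. It stands in for the planned mixed logistic model at a single time point.

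Example: c = 5%, f = 10%, g = 0 gives 0.05 + 0.95·0.10 = 14.5% v 5.0%.

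**Chance of a significant false effect, c = 5%:**

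| Over-reporting, intervention (f) | Reported rate, intervention | g = 0% (control reports 5.0%) | g = 2% (6.9%) | g = 5% (9.75%) |
|---|---|---|---|---|
| 10% | 14.5% | 20.7% | 10.5% | 3.5% |
| 20% | 24.0% | 71.1% | 54.3% | 32.2% |

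With g = 0, f = 5% gives 4.8% and f = 15% gives 46.1%. With f = 10% and g = 0, a true rate of 3% gives 27.6% and a true rate of 10% gives 11.6%.

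The answer depends on the gap between f and g, not on f alone. If both arms over-report equally (f = g = 5%), the rate is 0.9%, in line with the nominal 1%.

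**What a cotinine/nicotine check would do.** Take the worst cell (f = 20%, g = 0). Assume 90% of true quitters and half of false quitters pass.

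- intervention: 0.05·0.90 + 0.95·0.20·0.50 = 14.0%
- control: 0.05·0.90 = 4.5%
- false-positive rate: 22%, against 71% without the check

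**Cost of the check when reporting is honest.** Suppose f = g = 0 but true quitters pass more often in the intervention arm (95% v 80%). At c = 5% the counted rates are 4.75% v 4.0%, and the false-positive rate is 0.4%. At c = 10% they are 9.5% v 8.0%, and it is 1.1%. The check adds almost no error of its own in these cases.

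**The case against.** Four points can be made against the concern.

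1. **The protocol contains no error or contradiction here.** It promises verification for the child's exposure and never for parental smoking. Cessation is secondary and optional in counselling, and how a self-reported result is labelled is often left to a fuller document. This stands, and it is why the point is minor. The measurement schedule itself is stated, however, and includes no test of the parents, so later analysis wording can only limit the claim.

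2. **Pressure to over-report does not act in one arm only.** All families learn the study's aim before randomisation, the Discussion expects the invitation to influence controls, and intervention parents are told they need not quit. This stands. A reader might take 71%, the zero-control-over-reporting figure, as the size of the problem; the documents do not support that, and the range must include over-reporting by controls.

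3. **Child cotinine does not measure parental abstinence.** A reader might infer that the existing samples could verify quitting. They cannot: the protocol itself says exposure can fall because parents smoke outside, and the Discussion allows smoking in a room the child does not enter. A high value can contradict a claim; a low value cannot confirm one. Nor is there a rule to borrow, because the article states no cotinine cut-off even for the primary outcome.

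4. **The check can leak unequally.** If the intervention lowers children's exposure, continuing smokers in that arm will pass more often. This also stands. In the example above the check leaves 22%, far above 1%, so it cannot carry a cessation claim as proof. It is still a clear improvement on 71%.

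**Conclusion.** The point holds as a minor one. Question 2 would be answered from self-report in an unblinded trial that counsels one arm, and unequal over-reporting can produce a false cessation effect that the 1% level does not prevent. With 63 families per arm and 5% true cessation in both, 10–20% over-reporting in the intervention arm gives a false-positive rate of 21–71% with none in controls, 10.5–54% with 2%, and 3.5–32% with 5%. All misreporting and cessation rates are assumptions.

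A reader might infer that a cessation effect from this trial would be spurious. The documents do not show that: they give no evidence that misreporting occurs, or how it differs by arm. A reader might also extend the doubt to the primary outcome; that comparison is checked against the child's cotinine and is not affected by this point.

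**What to change.** Before the data are seen, write the following into the analysis of question 2:

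1. Keep the questionnaire result, and label it 'self-reported cessation'.
2. Add a second analysis, the same in both arms and per family (the unit randomised). It counts a family as non-quitting when the child's urine cotinine at that visit, or household nicotine at month 12, contradicts the claim. Fix and state the cut-offs in advance.
3. Call this result 'self-reported, not contradicted by cotinine/nicotine', not 'verified'.
4. Claim no cessation effect from the questionnaire alone. If the two analyses disagree, draw no cessation conclusion. If they agree, state that the evidence is still self-report.

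**Cost.** No new sample or visit; the work is choosing the cut-offs and a few lines of analysis text.

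**Downsides.** The check is partial. Parents who smoke only outdoors can pass, possibly more often in the intervention arm, and a true quitter whose child is exposed elsewhere is missed. Household nicotine helps only at month 12, because the only other measurement is at baseline.

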#### Household nicotine measurements

Household nicotine levels are measured (at baseline and 12 months after baseline) by placing a passive sampling diffusion monitor in the living room area [34]. The monitors are placed in the homes and removed one week later. The household nicotine concentrations levels are analysed by means of gas chromatography at the University of California at Berkeley School of Public Health.

#### Airway inflammation and oxidative stress

Non-invasive parameters of airway inflammation and oxidative stress are assessed (at baseline and 6 months after baseline) with the handheld exhaled breath condensate (EBC) sampling device Ecoscreen, (CareFusion, Germany). A nose-clip is used and children are instructed to breathe tidally through a mouthpiece with a two-way non-rebreathing valve during 10 minutes. Saliva contamination is prevented by a saliva trap. Children are distracted by watching a video or by playing on a portable gaming device. After 10 minutes the condensate is collected in 1.5 ml Eppendorf tubes (original Eppendorf Protein LoBind Tube). Tubes are filled with 100 μl of condensate, depending on the amount of condensate acquired during collection. Directly after, acidity (pH) of the EBC is measured with pHenomenal pH-1000H (VWR Int., Leuven, Belgium). A minimum of 150-200 μl of EBC is needed for the pH measurement. The Eppendorf tubes are frozen with dry-ice, directly after pH-measurement and are stored at −80 °C. The condensate is analysed for markers relevant for asthma and airway inflammation (IL-4, IL-5, IL-6, IL-8, IL-10, IL-12p70, IL-13 and TNF-α) [35] as described in earlier studies.

#### Wheezing

Possible presence of wheezing is measured (at baseline and 6 months after baseline) with a non-invasive handheld instrument, Wheezometer^TM^ (KaramelSonix Ltd). The Wheezometer is placed behind the manubrium while the child is asked to breathe normally. Breath sounds from the trachea are recorded during 30 seconds and in case wheezing is present, it is presented as a wheeze rate (Tw/Ttot%).

#### Lung function: measuring airway resistance in children ≤5 years of age

In children aged 5 years and younger, measurements of airway resistance are performed (at baseline and at 3, 6, 9, and 12 months after the baseline measurement) by means of the MicroRint (Micro Medical, Rochester Ltd, UK) [36]. Children are asked to sit in an upright position and to breathe normally through a facemask. Their attention is diverted by video clips to guarantee tidal breathing as much as possible. Five airflow interruptions are made on the peak flow of expiration, the median MicroRint value together with the flow and pressure curves are displayed. The median MicroRint value is used for analysis. Afterwards, 300 microgram of salbutamol (Airomir®, Teva Pharma NL, Haarlem, the Netherlands) is inhaled through the AeroChamber® (Trudell Medical International, Ontario, Canada). After 15 minutes, MicroRint measurements are repeated to assess the reversibility to the salbutamol.

#### Lung function: dynamic spirometry in children 6–13 years of age

In children aged 6–13 years, dynamic spirometry is performed (at baseline and at 3, 6, 9, and 12 months after the baseline measurement) by means of the Flowhandy Zan 100USB® (nSpire Health GmbH, Germany). The ZAN-100 pulmonary spirometer is attached to a laptop making it possible to perform home-based measurements. Standard spirometry references are created by entering age, weight, length and sex of the child. Children are instructed and motivated before and during measurement. Younger children, below 7–8 years of age, are stimulated to perform better by using motivational images. A maximum of 8 maximal expiratory flow volume (MEFV) curves are performed, until three technically satisfactory measurements are achieved (ATS/ETS criteria). Thereafter, 300 microgram of salbutamol (Airomir®, Teva Pharma NL, Haarlem, the Netherlands) is inhaled. After 15 minutes, MEFV curves are measured as described earlier to assess the reversibility to salbutamol. The highest forced expiratory volume in one second (FEV_1_), forced vital capacity (FVC), and maximal expiratory flow at 50% FVC (MEF_50_) are used for analysis. The FEV_1_ is expressed as a percentage of the predicted value (gender, age, ethnicity, weight, height, ambient temperature, humidity and barometric pressure taken into account).

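### Taking the highest MEF50 favours blows ended early, which makes this secondary outcome more sensitive to effort than it need be

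*Protocol article*

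**What the plan says.** The section on dynamic spirometry in children aged 6–13 gives one selection rule for three indices: "The highest forced expiratory volume in one second (FEV_1_), forced vital capacity (FVC), and maximal expiratory flow at 50% FVC (MEF_50_) are used" for analysis. On its natural reading, each index is the largest value found across the child's curves. Nothing ties MEF50 to the curve with the best FVC or the best FEV1+FVC.

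On the number of curves, the same section says: "A maximum of 8 maximal expiratory flow volume (MEFV) curves are performed, until three technically satisfactory measurements are achieved", with reference to published acceptability criteria. It does not say whether the highest value is sought among those three curves or among all attempts.

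Effort is coached, and "Younger children, below 7–8 years of age, are stimulated to perform better by using motivational images". Spirometry is done at all five visits. After salbutamol, "MEFV curves are measured as described earlier to assess the reversibility to salbutamol", so the same rule applies before and after the bronchodilator.

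Three other places bear on the point. The Control group section gives both arms the same measurement protocol and schedule. The Randomisation section states: "Blinding of participants or members of the research team for this study is not possible". The Statistical methods section tests secondary outcomes between arms at a 1% level.

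**The concern.** FEV1 and FVC are bounded by what the child can blow. A child who stops early loses FVC and gains no FEV1, so the largest value comes from a better effort.

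MEF50 behaves differently because its reference point moves with the blow. Flow falls as the lung empties. If the blow ends early, measured FVC is smaller, the 50% point comes sooner, and the flow there is higher. A rule that picks the largest MEF50 therefore leans towards blows that ended early.

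At stake is what MEF50 measures. Its level, its change between visits and its response to salbutamol would partly reflect how fully the child emptied the lungs on the selected blow. Lung function is named in the third secondary research question, and effort in 6- to 13-year-olds tested at home can be expected to vary. If staff who know the allocation coached the two arms differently, part of that difference would also reach the comparison between arms.

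**Working it through.** **Plan's own figures.** The article gives no figure for MEF50 to reproduce. Its one worked calculation concerns the primary outcome: 10% against 30%, two-sided 5%, 80% power. Pooled variance without continuity correction gives 62 per arm, or 124, against the stated 126; and 126/0.85 = 148.2, against 148. That calculation is sound and not involved here.

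**Inputs from the article.** The highest-value rule, the stop at three satisfactory curves, and the cap of eight attempts.

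**Inputs assumed, because the article gives none.** Shape of the descending limb: linear. Early-stop shortfall r: uniform on 0–5% or 0–10% of FVC. Other blow-to-blow variation in flow: 3% (CV).

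**Step 1: one blow.** Let v be the volume exhaled as a fraction of true FVC, and flow = k(1 − v).
- Complete blow: 50% point at v = 0.5, flow = 0.5k.
- Blow ended early by r: measured FVC is 1 − r, the 50% point is v = (1 − r)/2, and flow = k(1 + r)/2. MEF50 is multiplied by (1 + r): +5% for r = 5%, +10% for r = 10%.
- Curved limb, flow proportional to (1 − v)^1.3: the factor is (1 + r)^1.3, giving +6.5% and +13.2%.
- Incomplete inspiration by s: the blow starts at v = s, the midpoint is (1 + s)/2, and the factor is (1 − s). This lowers MEF50, so the problem is confined to early termination.

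**Step 2: three blows, no other noise.** The mean of the largest of three uniform values on (0, a) is 3a/4, and of the smallest a/4.
- Highest MEF50: 3 × 5%/4 = 3.75% and 3 × 10%/4 = 7.5% too high.
- MEF50 from the most complete blow: 5%/4 = 1.25% and 10%/4 = 2.5% too high.
- For 0–10%, the blow chosen by the highest-value rule has mean FVC 1 − 0.075 = 0.925 of true, against 0.950 over all blows.

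**Step 3: three blows with 3% noise (simulation).**

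| Shortfall | Highest MEF50 | Most complete curve |
|---|---|---|
| 0–5% | +5.4% | +1.3% |
| 0–10% | +8.7% | +2.5% |

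The most complete curve is the one with the largest FVC. It stands in for the largest FEV1+FVC, since a blow cut short after the first second keeps its FEV1.

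Not all of the middle column comes from early stopping. With fully complete blows, the highest of three exceeds the truth by 0.846 × 3% = 2.5%, because the expected largest of three standard normal values is 0.846.

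**Step 4: sensitivity to effort.** Moving from a 0–5% to a 0–10% shortfall shifts the highest-value rule by 8.7 − 5.4 = 3.3 points and the most complete curve by 2.5 − 1.3 = 1.2 points.

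**Step 5: both kinds of incomplete blow together.** Adding incomplete inspiration of 0–5% to the cases in Step 3 brings the highest-value bias down to about 3% and 6%. The most complete curve is then within about 1% of the truth.

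**The case against.** The strongest case against has five parts.

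1. **Quality requirement.** Curves must be technically satisfactory by named criteria, which limits how truncated an accepted blow can be. This stands. A 0–10% shortfall may be generous, and nothing in the article fixes it.

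2. **Number of attempts.** A reader might infer that MEF50 rises with the number of blows, up to eight. Under the same assumptions, the highest of eight would be 7.4% or 11.1% too high. The article does not support that reading as it stands: testing stops at three satisfactory curves, and eight caps the attempts. The count matters only if unsatisfactory curves are also eligible, or if a child fails to reach three. The text leaves both open.

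3. **Comparison between arms.** A reader might also infer that the randomised MEF50 comparison is biased. It is not, if effort is equal: both arms follow the same protocol, and a common upward shift cancels. Bias would need coaching or effort to differ by arm. An unblinded team makes that possible, but nothing shows it. Unequal coaching would also reach FEV1 and FVC, which the fix leaves alone.

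4. **Ordinary inflation of a maximum.** Any maximum of noisy values is too high, including that of FEV1 and FVC. This stands, and Step 3 separates it out. The part peculiar to MEF50 is the preference for blows ended early, which remains without noise (3.75% and 7.5%).

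5. **Condensed article.** Which curve supplies which index could be left to the full protocol. But the article does state a rule, and on its natural reading that rule covers MEF50. The point concerns that stated rule, not a missing one.

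**Conclusion.** The point holds in a limited form. Applied to MEF50, the highest-value rule favours blows ended early, because the index is read at half of each blow's own FVC; FEV1 and FVC have no such weakness. With three eligible blows the overstatement is about 5% or 9% for an assumed 0–5% or 0–10% shortfall with 3% noise, against about 1% to 2.5% for the most complete curve. These figures illustrate; they rest on the assumed shortfall, noise and linear limb. They are smaller if the quality criteria exclude most early stops or if incomplete inspiration is also common.

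The consequence is an MEF50 whose level, change over visits and reversibility depend on effort more than they need to. It is not a demonstrated bias between arms, and dependence on the number of attempts does not follow from the text. MEF50 is one of several secondary outcomes, measured only in the older children. The point is worth tidying up and no more than that.

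**What to change.** In the section on dynamic spirometry, keep the highest FEV1 and the highest FVC. State that MEF50 is taken from the single technically satisfactory curve with the largest sum of FEV1 and FVC, by the same rule before and after salbutamol, at every visit and in both arms. Naming technically satisfactory curves as the eligible ones for MEF50 also settles whether other attempts count.

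**Cost.** One sentence and no extra measurement, provided the values of each curve are kept; the article says the spirometer is attached to a laptop but does not describe storage. A single-curve MEF50 is slightly noisier: with three blows and 3% noise its standard deviation is about 3.2–3.6%, against 2.6–3.2% for the maximum.

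**Limits.** The change reduces sensitivity to effort without removing it (Step 4). FVC and MEF50 may still come from different curves, since the highest FVC is kept.
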